### Statistical analyses

Data will be analyzed according to the intention-to-treat principle (ITT). We will examine for differences in all primary and secondary outcome variables between the two study arms at baseline and follow-up assessments using (generalized) linear mixed models. We will specifically model repeated measures nested within participants and participants nested within treatment centers by defining respective random intercepts and slopes. Study conditions and time will be modeled as fixed effects. Appropriate distributions for non-normal continuous and/or count outcomes will be specified (e.g., negative binomial, zero-inflated, Poisson). Subject to the sample’s actual gender distribution, we will investigate the intervention’s gender-specific effects by including a gender*treatment*time interaction term. If this is not possible due to inadequate sample size (i.e., the model is not identifiable), separate subgroup analyses will be run, which will allow the determination of differential treatment effects.

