### Assessments

#### Primary and secondary outcomes

The primary outcomes will be the percentage of negative urine tests for illicit, non-prescribed use of opioids (opium, heroin, tramadol) between each measurement point (baseline, 1-, 2-, 3-, 6-, and 12-month follow-up) and treatment retention indicated by weekly percentage of participants who continue participation defined as receiving planned services (i.e., opioid agonist medication, physician’s visits, counselling sessions) and completing the study assessments. Secondary outcomes will be the longest period of abstinence for illicit, non-prescribed use of opioids (opium, heroin, tramadol) confirmed by urine samples; the number of self-reported other-street-drug free days over the preceding 7 days (Timeline Follow Back method) [TLFB], [21]; the number of self-reported opioid-free days over the preceding 7 days [TLFB]; the number of missed OMT appointments; screening of methamphetamine use via monthly urine tests; identification of benzodiazepine use through monthly urine screenings; detection of THC presence via monthly urine analyses; changes in communicable disease risk-taking behaviors (Blood-borne Virus Transmission Risk Assessment Questionnaire) [BBV-TRAQ], [22]; HIV test results; symptoms of stress (Perceived Stress Scale) [PSS-10], [23] and other common mental health symptoms, such as depression (Patient Health Questionnaire) [PHQ-9], [24], anxiety (Generalized Anxiety Disorder Screener) [GAD-7], [25]; PTSD (International Trauma Questionnaire for PTSD) [ITQ] [26]; adult attention-deficit/hyperactivity disorder symptoms interview [NSC-R]; alcohol use disorder symptoms (Alcohol Use Disorders Identification Test) [AUDIT] [27]; nicotine dependence (Fagerstrom Test for Nicotine Dependence) [FTND] [28], and, client satisfaction (Client Satisfaction Questionnaire [CSQ-8], [29]. Assessments will be conducted by the participating psychologists, who will assist the patients with the input of the relevant data in the web-based questionnaires.

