Furthermore, any negative effects due to the smartphone intervention will be measured via the Negative Effects Questionnaire [30] at all follow-up assessments. As an indicator of treatment adherence, data will be collected on how many modules have been completed and how many OMT physicians’ visits and counseling sessions are attended by each participant. The primary and secondary outcomes and the exact time points at which each measure will be applied are presented in Table 2.

**Table 2 Tab2:** Overview of measures and their time of assessment

	Baseline	Month 1	Month 2	Month 3	Month 6	Month 12
Sociodemographic characteristics	x					
Addiction treatment history	x					
Percentage of negative urine tests (illicit, non-prescribed opioids)		xxxx	xxxx	xxxx	x	x
The longest period of abstinence from the illicit opioids		x	x	x	x	x
Number of missed OMT appointments		x	x	x	x	x
Blood-borne Virus Transmission Risk Assessment Questionnaire (BBV-TRAQ)	x			x	x	x
Number of self-reported opioid use/free days - (TLFB)	x	x	x	x	x	x
Self-reported other street-drug use/free days - (TLFB)	x	x	x	x	x	x
Perceived Stress Scale (PSS-10)	x			x	x	x
Patient Health Questionnaire for Depression (PHQ-9)	x			x	x	x
Generalized Anxiety Disorder Screener (GAD-7)	x			x	x	x
International Trauma Questionnaire for PTSD (ITQ)	x			x	x	x
Client Satisfaction Questionnaire (CSQ-8)		x	x	x	x	x
Negative Effects Questionnaire		x	x	x	x	x
Methamphetamine (MA) urine test (monthly)	x	x	x	x	x	x
Benzodiazepine urine test (monthly)	x	x	x	x	x	x
THC urine test (monthly)	x	x	x	x	x	x
HIV test result	x			x	x	x
Adult ADHD Interview (NSC-R)	x					
Alcohol Use Disorder Identification Test (AUDIT)	x			x	x	x
Fagerstrom Test for Nicotine Dependence (FTND)	x			x	x	x

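### HIV test status is compared between arms in all participants, including any already positive at baseline, although only those negative at baseline can show a treatment effect

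*Protocol article*

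**What the plan says.** In the protocol article, the section on primary and secondary outcomes includes, in its list of secondary outcomes, "changes in communicable disease risk-taking behaviors (Blood-borne Virus Transmission Risk Assessment Questionnaire) [BBV-TRAQ], [22]; HIV test results". The HIV item is a status at a visit. Seroconversion or new infection is not mentioned. The Table 2 row "HIV test result" is marked at baseline and months 3, 6 and 12.

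The Statistical analyses section exempts no outcome: "We will examine for differences in all primary and secondary outcome variables between the two study arms at baseline and follow-up assessments using (generalized) linear". The class of model named there is the mixed model. The analysis set is stated as "Data will be analyzed according to the intention-to-treat principle (ITT"). Repeated measures are nested in participants and participants in centres, with random intercepts and slopes. On the fixed part it says: "Study conditions and time will be modeled as fixed effects". A treatment-by-time term appears only inside the three-way interaction with gender.

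The two exclusion criteria are other substance dependence (except tobacco) and current severe or acute psychiatric disorder. HIV infection is neither an exclusion criterion nor a stratum. The Introduction gives non-sterile syringes as the route for 57.3% of registered HIV cases, but no HIV prevalence or incidence for patients entering opioid maintenance therapy.

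**The concern.** HIV positivity is an absorbing state. Anyone positive at baseline is positive at months 3, 6 and 12 in either arm, and PROMPT cannot change that. Only participants negative at baseline can respond. Each person's series is therefore all negative, all positive, or a single step from negative to positive, which leaves a subject-level slope almost nothing to estimate. The urine screens and symptom scales under the same rule can move in both directions, so the rule suits them better.

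Preventing communicable disease is part of the trial's rationale, and Module 5 addresses blood-borne viruses, so readers will take the HIV comparison as evidence on that aim. As written, an arm difference at month 12 mixes the chance split of old infections at randomisation with any effect on new ones.

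**Working it through.** **Plan's own figure.** The document states no number for HIV. Its sample size (N = 400, 80% power, d = 0.35, 30% dropout) belongs to the general mixed model and has no bearing here. Only N = 400 and 1:1 allocation are used, giving 200 per arm.

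**Assumptions.** Baseline prevalence *p* and annual new-infection risk *q* are not in the document, so ranges are shown. A rate *r* per person-year converts to *q* = 1 − exp(−*r*). Dropout is ignored unless stated.

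**Step 1: who makes up the month-12 positives.** Prevalent = 400*p*; new = 400(1 − *p*)*q*; prevalent share = prevalent / (prevalent + new).

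| Prevalence | Incidence or risk | Prevalent | New | Prevalent share |
|---|---|---|---|---|
| 5% | 1 per 100 person-years (*q* = 0.00995) | 20 | 380 × 0.00995 = 3.8 | 20/23.8 = 84% |
| 2% | 2% a year | 8 | 392 × 0.02 = 7.8 | 8/15.8 = 51% |
| 2% | 3% a year | 8 | 392 × 0.03 = 11.8 | 8/19.8 = 40% |
| 1% | 2 per 100 person-years | 4 | 7.8 | 34% |
| 15% | 0.2 per 100 person-years | 60 | 0.7 | 99% |

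The last two rows are the extremes of a grid with prevalence 1% to 15% and incidence 0.2 to 2 per 100 person-years. If PROMPT halved a 3% risk in its own arm, the third row would have 196 × 0.03 + 196 × 0.015 = 8.8 new cases, still more than the 8 prevalent ones.

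**Step 2: chance imbalance from prevalent cases.** The SD of the arm difference at baseline is √(2 × 200 × *p*(1 − *p*)). At 2% this is √7.84 = 2.8 cases; at 5% it is √19 = 4.4 cases. In simulation at 5% and 1 per 100 person-years, baseline imbalance accounted for 83% of the variance of the month-12 arm difference (34% to 99% over the grid).

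**Step 3: what the model coefficients follow.** A random-intercept logistic model was simulated 150 times with visits at 0, 3, 6 and 12 months, N = 400, 5% prevalence, 1 per 100 person-years and no treatment effect.

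| Coefficient | Correlation with baseline imbalance | Correlation with arm difference in new infections |
|---|---|---|
| Arm (condition and time only) | 0.50 | 0.20 |
| Arm-by-time (when fitted) | −0.34 | 0.89 |

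The consequence therefore depends on which contrast is read.

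**Step 4: what remains after restricting to baseline-negatives.** With 190 per arm (200 less 5%), exact power of a two-sided 5% Fisher test (alpha is assumed; none is stated) for a halved risk is:
- 1% v 0.5%: 0.5%
- 2% v 1%: 4.0%
- 3% v 1.5%: 8.2%

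If 30% dropout leaves 190 × 0.7 = 133 per arm, these become 0.1%, 1.6% and 4.4%. Restriction makes the result interpretable but leaves it too sparse for a test.

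**The case against.** The strongest reply is that the analysis paragraph is a condensed catch-all. It cannot be literal for every listed outcome: the ADHD interview is a secondary outcome but is measured only at baseline. Event definitions for a rare binary outcome are commonly left to a statistical analysis plan that is not shown. That has force against complaints about missing detail. Here, however, the article itself states the outcome as a status, the analysis set, the model family and its application to all secondary outcomes, and that combination does not suit a permanent state.

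Second, the tested contrast might be treatment-by-time. The gender interaction would ordinarily bring in that lower-order term, and the sample size is built on change over time. Step 3 shows that this contrast would mostly follow new infections. This stands as a limit on the point. But the article does not state that contrast for HIV, and a handful of events does not suit a random-slope model in any case.

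Third, a reader might infer that prevalent infections, and not new ones, drive the comparison, or that it is biased. The document supports neither. It gives no prevalence or incidence, and Step 1 shows new cases in the majority under plausible assumptions. Randomisation makes prevalent cases noise and dilution that favour no arm systematically, and the baseline test would show any imbalance.

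Fourth, the protocol claims no power for HIV, so low power is not in itself an error. That is accepted: Step 4 supports descriptive reporting and nothing more. A failure of the model to converge is possible but was not demonstrated.

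**Conclusion.** The point holds as a minor correction to one secondary outcome. The stated rule compares HIV status in everyone randomised, although participants positive at baseline cannot contribute to a treatment effect. How far they cloud the comparison is unknown from the document: under assumed rates, prevalent cases make up anywhere from 34% to 99% of month-12 positives, with 84% at 5% prevalence and 1 per 100 person-years and about half or less at 2% prevalence with 2% to 3% annual risk. The conclusion that baseline positives are uninformative needs no assumed rate, only that positivity is permanent and that such patients may enrol. Neither primary outcome is affected.

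**What to change.** In the outcome list, replace "HIV test results" with new HIV infection (seroconversion) by month 12 among participants HIV-negative at baseline. In the Statistical analyses section, take this outcome out of the mixed-model rule. State that counts by arm, with an exact confidence interval for the risk difference, will be reported as descriptive or exploratory, and that the trial is not expected to support a conclusion on HIV incidence. Report baseline HIV status by arm alongside. Leave BBV-TRAQ, already scheduled at the same four visits, as the inferential communicable-disease outcome.

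The cost is about one sentence in each of the two sections. No new data are needed, because the baseline test is already scheduled. The downside is one fewer inferential secondary outcome.

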### Eligibility criteria

Patients will be eligible for the study if they meet the following criteria: (1) current diagnosis of opioid dependence (ICD-11), (2) receiving methadone or buprenorphine maintenance treatment for at least two weeks and not more than eight weeks, (3) ownership of a smartphone, (4) access to the Internet, (5) minimal age of 18 years, (6) provide written informed consent, (7) good command of and ability to read and write Persian. Exclusion criteria are (1) concurrent diagnosis of any other substance dependence (except tobacco) and (2) current severe or acute psychiatric disorders.

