### Sample size

Based on the results of a systematic review and meta-analysis on internet interventions in adults with opioid dependence [17], we expect a Cohen`s d of about 0.35, comparing Study arm 1 (PROMPT) and Study arm 2 (OMT as usual). An overall sample size of N = 400 participants would have 80% power to detect the expected effect size when modeling a three-level generalized linear mixed model with six measurements (baseline, 1-, 2-, 3-, 6-, and 12-month follow-up) and eight treatment centers. Respective indices of baseline variance at the participant and treatment center level, as well as slope variance at the center level, and moderate heterogeneity in change over time, were based on a psychotherapeutic simulation study [18]. This calculation also considers an expected dropout rate of 30%, with a higher risk of dropout towards the end of the study. Calculations were performed using the package powerlmm in R [19].

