## Discussion

This study aims to investigate the effectiveness of blended OMT treatment in which OMT as usual, is delivered in combination with a smartphone intervention for patients with opioid dependence in Iran.

The prevalence and burden of OUD in Iran, both on an individual and societal level, warrant a variety of effective treatment strategies. So far, research on the effectiveness of digital interventions for the treatment of OUD is primarily limited to add-on interventions that have been investigated in the United States [31]. However, the scientific evidence on the value of, in particular, blended interventions in developing countries for the treatment of OUD is scarce.

Through the integrated approach of blended interventions, we expect to provide our participants with both the benefits of digital interventions and the advantages of face-to-face therapy. However, there are many unknowns regarding blended interventions, such as how to combine these treatment modalities and the characteristics of therapist support. Our study will attempt to provide relevant answers to these questions. Furthermore, we will better understand to what extent the blended intervention suits patients in OMT settings by exploring treatment adherence, dropout, and satisfaction with the blended intervention. In addition, by monitoring the activities of our patients in the smartphone intervention (e.g., time spent in each module), we will be able to get insights into what happens during the treatment period. This will further increase our knowledge of the suitability of blended treatments for patients in OMT.

We will not interfere with the current practices of OMT as usual. By permitting the practice of usual care for OMT patients, the generalizability of our results is enhanced. Given the heterogeneity of OMT as usual, this could also be regarded as a limitation. However, since our study is designed to be a pragmatic trial, we aim to compare the effectiveness of the blended intervention with the current OMT as usual practice. Therefore, OMT as usual will be monitored carefully to control for potential confounding effects.

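### The planned between-arm comparison at baseline is uninformative, and impossible for both primary outcomes; how baseline and post-randomisation care enter the model should be settled

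*Protocol article*

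**What the plan says.** The Statistical analyses section of the protocol article states: "We will examine for differences in all primary and secondary outcome variables between the two study arms at baseline and follow-up assessments". The tool is a (generalized) linear mixed model under intention to treat. On its terms the section says "Study conditions and time will be modeled as fixed effects" and "We will specifically model repeated measures nested within participants and participants nested within treatment centers by defining respective random intercepts and slopes". The only interaction written out is the one for gender, "including a gender*treatment*time interaction term". No baseline covariate and no post-randomisation covariate is named.

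The Sample size section counts baseline as a modelled response: "six measurements (baseline, 1-, 2-, 3-, 6-, and 12-month follow-up) and eight treatment centers". The Randomization section places the baseline assessment before allocation. In Table 2 the row "Percentage of negative urine tests (illicit, non-prescribed opioids") has its first entry at month 1, and the baseline cell is empty.

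The Discussion, commenting on the heterogeneity of usual care, adds that "OMT as usual will be monitored carefully to control for potential confounding effects". No variable or model is attached to that remark.

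**The concern.** There are three linked points.

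- **The comparison at baseline.** Randomisation follows the baseline assessment, so any difference between arms at baseline is chance. Examining it answers no question about PROMPT. The sentence also covers all outcomes, although several, including both primary outcomes, have no baseline value.
- **How baseline enters the model.** With baseline as a response and an unrestricted arm difference there, the condition-by-time contrast at a follow-up is in effect a difference in change scores. That is less precise than using the same baseline as a covariate or holding the arm means equal at baseline.
- **Care delivered after randomisation.** In a randomised comparison this care is not a confounder. It can be altered by PROMPT, and it is part of the retention outcome. If it entered an effectiveness model, the estimate would no longer be the intention-to-treat effect.

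At stake are avoidable loss of precision on the secondary outcomes, a risk that chance baseline differences are over-read, and an opening for an adjustment that would distort the treatment effect.

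**Working it through.** **1. The plan's own figure.** The article gives N = 400 for 80% power at d = 0.35 with 30% dropout. The variance components are taken from a cited simulation study and are not printed, so N = 400 can be neither reproduced nor refuted. A plain two-group formula (two-sided 5%, assumed) gives 129 per arm, 258 in total, and 258 / 0.70 = 369 after dropout. Nothing below depends on N = 400 being right.

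**2. Outcomes against the Table 2 schedule.**

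- No baseline entry: opioid urine outcome (primary), longest abstinence, missed appointments, CSQ-8.
- Retention (primary) has no row in Table 2 and has no meaning before follow-up starts.
- Baseline entry present, 14 measures: BBV-TRAQ, two TLFB counts, PSS-10, PHQ-9, GAD-7, ITQ, three urine screens (methamphetamine, benzodiazepine, THC), HIV, NSC-R, AUDIT, FTND. The NSC-R is taken at baseline only, so it has no follow-up to compare.

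If each of the 14 were tested at 5% (assumed), 14 × 0.05 = 0.70 chance differences would be expected. If they were independent (also assumed), the chance of at least one is 1 − 0.95^14 = 51%.

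**3. Precision for outcomes with a baseline.** Take one follow-up, equal variances, and correlation ρ between baseline and follow-up (assumed; the article gives none). Relative to the variance of a follow-up-only contrast:

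- change score, or free baseline difference: 2(1 − ρ)
- baseline as covariate, or equal baseline means: 1 − ρ²
- ratio: (1 − ρ²) / [2(1 − ρ)] = (1 + ρ)/2

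The power columns use d = 0.35, two-sided 5%, and 400 × 0.70 = 280 completers, 140 per arm.

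| ρ | 2(1 − ρ) | 1 − ρ² | Ratio | Variance saved | Power, free baseline | Power, adjusted |
|---|---|---|---|---|---|---|
| 0.4 | 1.20 | 0.84 | 0.70 | 30% | 76.2% | 89.2% |
| 0.5 | 1.00 | 0.75 | 0.75 | 25% | 83.4% | 92.2% |
| 0.6 | 0.80 | 0.64 | 0.80 | 20% | 90.6% | 95.5% |
| 0.7 | 0.60 | 0.51 | 0.85 | 15% | 96.6% | 98.4% |

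A follow-up-only analysis would have 83.4% throughout, so below ρ = 0.5 the free-baseline contrast is worse than ignoring baseline. These figures illustrate secondary outcomes only.

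**4. Post-randomisation care.** The Primary and secondary outcomes section defines retention through receipt of medication, physician visits and counselling, plus completion of assessments. Attended visits and sessions are also the adherence measure. The intervention sections make counselling the place where PROMPT modules and tracker data are discussed. Adjusting for attendance would therefore condition retention on its own components and, for other outcomes, remove whatever part of the effect runs through attendance. With an effect a of arm on attendance and b of attendance on outcome, the adjusted effect is 0.35 − ab when nothing else links attendance and outcome. For a of 0.2 to 0.5 and b of 0.2 to 0.4 it lies between 0.35 − 0.04 = 0.31 and 0.35 − 0.20 = 0.15. In simulation with one unmeasured shared cause it lay between 0.29 and 0.11. All these path sizes are assumptions.

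**The case against.** Baseline as a repeated response in a mixed model is an accepted way to use it, and the article does not say that baseline means are left unconstrained. It speaks of examining differences within the models, not of a significance test at baseline. Covariate lists are commonly left to a statistical analysis plan, which is not shown. Centre is already in the model. The precision formula is for a single follow-up and does not describe a multi-occasion model with random slopes. It also cannot reach the primary outcomes, which have no baseline. All of this stands and limits the point: the absence of named covariates is no defect, and the covariates are a recommendation.

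Three stronger readings are tempting, and the article does not support them:

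- **A covariate plan turned round, with baseline ignored and later care adjusted for.** The Discussion sentence is a general remark about monitoring. The Statistical analyses section contains no post-randomisation covariate.
- **A treatment effect diluted by averaging in baseline.** With a pooled condition effect, a constant effect would shrink by 1/4 over four occasions or 1/6 over six. The gender-by-treatment-by-time term and a power model built on slopes both point to a condition-by-time contrast, to which this does not apply.
- **A collapse in power.** If 40% of d = 0.35 ran through attendance and attendance were adjusted for, d would be 0.21 and, with a standard error of √(2/140) = 0.1195, power would fall from 83% to 42%. The 40% has no source and the adjustment is not planned, so the figure is hypothetical.

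The objection does not rescue the literal sentence, which announces a comparison at baseline for outcomes that have none there.

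**Conclusion.** The point holds in a limited form.

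- The stated comparison at baseline is uninformative because baseline precedes randomisation, and it conflicts with Table 2 for both primary outcomes. This rests on the text alone.
- For outcomes with a baseline, leaving the arm difference free there wastes precision. The variance would be 15% to 30% smaller with adjustment or equal baseline means, for ρ of 0.7 to 0.4. This assumes a single follow-up, equal variances and the stated range of ρ, and applies to secondary outcomes only.
- Controlling for usual care delivered after randomisation would not estimate the intention-to-treat effect, if it were carried out. The article does not commit to it, so this is a clarification and no size can be attached.

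The change is worth making before analysis because it is nearly free. It does not put the validity of the trial in doubt.

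**What to change.** 1. Delete the between-arm comparison at baseline, describe baseline by arm, and reconcile the coverage of all outcomes with Table 2, including the NSC-R, which has no follow-up.
2. For each outcome with a baseline, either constrain the arm means to be equal at baseline or enter baseline as a covariate. Write out the condition-by-time term and name its follow-up contrasts as the treatment effect.
3. For the two primary outcomes, add covariates collected or known at entry, for example TLFB opioid-free days, time already in OMT (eligibility allows "for at least two weeks and not more than eight weeks") and agonist medication at randomisation. Fix the list in advance and keep centre as already modelled.
4. State that OMT care delivered after randomisation is described by arm and is not a covariate in any effectiveness analysis. Reword the Discussion sentence to match.

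The cost is wording in the analysis section and slightly more model specification. No new data, visits or participants are needed.

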## Introduction

Iran has a high prevalence rate of opioid use. The 12-month prevalence of opioid use in the population aged between 15 and 64 is reported to be over 3.0%, and the 12-month prevalence of DSM-5 diagnosis of opioid use disorder (OUD) is 2.23% [1]. The gender gap in regard to opioid use in Iran is much larger compared to other countries [2, 3], which is likely due to socio-cultural factors [4, 5].

Over the past decades, consumption patterns have evolved from opium smoking – that still has a historical tradition – to heroin smoking and heroin injection, which has considerably increased the health consequences of opioid use in Iran [6, 7]. In fact, using non-sterile syringes is the most prevalent route (57.3%) of HIV transmission among all registered HIV-positive cases until the end of 2021 [8]. Furthermore, high prevalence rates for hepatitis C [7] and tuberculosis [9–11] have been reported among people who inject drugs in Iran.

Opioid maintenance therapy (OMT), using methadone and buprenorphine, was therefore introduced to respond to the HIV epidemic among those using opioids and scaled up rapidly [12, 13]. OMT programs are provided through a network of certified drug treatment centers and have shown promising effects for the treatment of OUD and for reducing the risk of HIV transmission [14–16]. However, there are limited resources to provide continuous psychosocial interventions necessary for the treatment of OUD and the management of common mental health symptoms, such as depression and anxiety, which are highly prevalent in patients with OUD [1].

Smartphone interventions for patients with OUD could help to close this gap by delivering psychological interventions with high fidelity while requiring fewer human resources and empowering individuals to self-manage mental health issues. The perceived anonymity, timeliness of access, and flexibility offered by digital interventions also evade commonly identified barriers to accessing care. Blended interventions that integrate face-to-face and digital interventions for patients with OUD could help to reduce this treatment gap. This study aims to develop a smartphone intervention and to deliver it in a blended treatment format for patients with OUD who enter OMT program and assess its effectiveness through a randomized controlled trial.

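### The fallback for gender effects does not test a gender difference, so the claim that it determines differential treatment effects is wrong as written

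*Protocol article*

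**What the plan says.** The Statistical analyses section of the Protocol article plans, depending on how many men and women are enrolled, to examine gender-specific effects "by including a gender*treatment*time interaction term". The model it extends is for "repeated measures nested within participants and participants nested within treatment centers by defining respective random intercepts and slopes".

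The fallback follows: "If this is not possible due to inadequate sample size (i.e., the model is not identifiable", then "separate subgroup analyses will be run, which will allow the determination of differential treatment effects". The section names no test or interval for the difference between the two gender-specific results, and it does not call the fallback exploratory.

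Two other places bear on the point. The Introduction states: "The gender gap in regard to opioid use in Iran is much larger compared to other countries". The Sample size section powers only the overall comparison: "we expect a Cohen`s d of about 0.35" and "An overall sample size of N = 400 participants would have 80% power to detect the expected effect size". No section gives the expected share of women in the trial.

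**The concern.** A differential effect is a difference between two effects. Two separate models give two effects, each tested against zero. Nothing in the plan takes the further step of comparing them, yet the text says that the question will thereby be answered.

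The trigger makes this worse. The rule applies only when the data are too thin for the interaction, and a separate model for the smaller gender rests on those same few participants. Given the Introduction's remark on the gender gap, the smaller gender is likely to be women, although that remark concerns opioid use in the population and not this sample.

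The protocol offers no other route from separate analyses to a gender claim. The natural one for a reader is to set a significant result in men beside a non-significant one in women. At stake is a published statement that the intervention works in men but not in women when the true effects are equal. The main treatment comparison is not at risk.

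**Working it through.** **Inputs from the Protocol article.** d = 0.35, N = 400, 80% power, 30% dropout, six measurements and eight centres (Sample size); 1:1 allocation (Randomization).

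**Assumed, because not stated.** Two-sided alpha 0.05. Share of women f = 2%, 5% or 10% (8, 20 or 40 of 400), with larger shares for comparison.

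**The plan's own figure.** The simple two-sample formula at d = 0.35 needs 129 per arm, 258 in total, or 258 / 0.7 ≈ 369 after dropout. The stated 400 comes from a three-level calculation in powerlmm whose variance inputs are not printed, so it can be neither reproduced nor called wrong. It leaves 400 × 0.7 = 280 completers against about 256 from the unrounded formula, an inflation of 280 / 256 ≈ 1.09, which is plausible. The stated 80% power is therefore taken as given below.

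**Step 1: can the fallback rescue an unidentifiable comparison?** With time as a six-level factor, the gender × treatment × time fixed effects have 2 × 2 × 6 = 24 columns, and a women-only treatment × time model has 12. With no women in one arm, the ranks are 18 of 24 and 6 of 12, so both fail. With at least one woman in each arm, both have full rank. On the fixed effects, the two models fail together. If the random intercepts and slopes are kept, a women-only model must also estimate its own variance components. At 5% women that is 20 / (8 × 2) = 1.25 women per centre and arm. A pooled model can share those components with men.

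**Step 2: if both gender models can be fitted, how often would significance disagree under equal effects?** 80% power corresponds to a noncentrality of 1.960 + 0.842 = 2.802. With the same true effect in both genders and information proportional to numbers:

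- men: θ = 2.802 × √(1 − f); women: θ = 2.802 × √f
- power = Φ(θ − 1.960) + Φ(−θ − 1.960)
- men significant, women not = power(men) × (1 − power(women))

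At f = 5%, θ is 2.731 in men and 0.627 in women. Power is 0.780 and 0.096, and 0.780 × 0.904 = 0.705. Adding the reverse pattern, 0.096 × 0.220 = 0.021, gives 0.726 in either direction.

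| Women | Power, men | Power, women | Men significant, women not | Discordant, either direction |
|---|---|---|---|---|
| 2% (8) | 0.792 | 0.068 | 0.738 | 0.752 |
| 5% (20) | 0.780 | 0.096 | 0.705 | 0.726 |
| 10% (40) | 0.757 | 0.144 | 0.649 | 0.683 |
| 20% (80) | 0.707 | 0.240 | 0.537 | 0.608 |
| 50% (200) | 0.508 | 0.508 | 0.250 | 0.500 |

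A simulation of 200,000 trials gave the same either-direction rates to within 0.002 at 5%, 10%, 20% and 50% women.

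**Step 3: dependence on the true effect.** For 5–50% women, discordance in either direction is 33–37% at d = 0.2 and 16% at d = 0.1. With no effect in either gender it is 2 × 0.05 × 0.95 = 9.5%.

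**Step 4: what a direct comparison would give.** A test of the difference between the two estimates had a simulated type I error of 4.9–5.0% at 5%, 10%, 20% and 50% women. Its power is low: if men had d = 0.35 and women no benefit, it is 7%, 9% and 13% at 2%, 5% and 10% women. The implied overall standard error is 0.35 / 2.802 = 0.125, so the 95% half-width for the gender difference is 1.96 × 0.125 / √(f(1 − f)), or about 1.7, 1.1 and 0.8 SD. Such an interval is wide, but it shows how little the data can say.

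**The case against.** The strongest reply is that the protocol never says a gender difference will be declared from discordant p-values. Separate estimates could be compared through their difference and its interval, and such detail is often left to a statistical analysis plan, which is not shown. This stands against any statement that separate analyses can never inform the question. It does not save the sentence, which asserts what the separate analyses will establish while planning no comparison.

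Three further objections have force.

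- Low power is not non-identifiability. With 40 women the fixed effects give no reason to use the fallback, so the 2–10% range is not shown to be where the rule would operate. Sparse cells, dropout or failure of the random effects could trigger it, most plausibly at the low end.
- The protocol does not say that the subgroup models keep all three levels. A reduced women-only model might be fitted where the full interaction model could not, so failure of the women-only model is not certain.
- Steps 1 and 2 are alternatives. If the women-only model cannot be fitted, there is no result in women to set against men; the discordance rates apply only if it can.

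A reader might infer that the fallback will usually produce a false gender difference. The documents do not support that. It needs a reading rule they do not state, a share of women they do not give, and a true effect near 0.35 in both genders. Calculating with all 400 completing raises the men-only rate to 73–86%, but that ignores the 30% dropout and the 80% power on which the protocol is built.

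**Conclusion.** The point holds in a limited form. As planned, the fallback does not by itself test a gender difference, so the claim attached to it is wrong. This needs no assumption about the share of women.

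The size of the risk is conditional. If a difference is read from discordant significance, a men-only finding would occur in about 65–74% of trials with equal true effects. That rests on d = 0.35 in both genders, the stated 80% power, two-sided alpha 0.05, 2–10% women and a normal approximation; alpha and the share of women are assumptions. The rate is much lower if the true effect is small.

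The consequence is a foreseeable and avoidable misstatement in a secondary analysis. The primary comparison, the sample size and the intention-to-treat analysis are untouched.

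**What to change.** Delete the clause claiming that the subgroup analyses determine differential effects, and replace the fallback with an ordered rule.

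1. If the three-way term cannot be fitted, fit a simplified pooled model that still estimates the gender difference in treatment effect, with variance components shared across genders. Two options are gender × treatment on follow-up values, adjusted for baseline where one is collected, or time reduced to a single linear or pre/post term with its interaction kept. Report the difference with its 95% CI, labelled exploratory.
2. If that also cannot be fitted, report results by gender descriptively and make no claim of a differential effect.

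Simply dropping time from the interaction is not enough. In a model whose repeated measures include baseline, a gender × treatment term would average arm differences over baseline and follow-up, and would not estimate a gender difference in treatment effect. Table 2 shows a baseline value for scales such as the PHQ-9 and GAD-7. It shows none for the percentage of negative opioid urine tests, so that outcome would need no baseline adjustment.

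The cost is a few lines of text. No data, visits or participants are affected.
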